### Statistical analysis

The number of falls per person-year will be analysed using negative binomial regression to estimate the difference in fall rates between the two groups, adjusted for previous multiple faller status and other confounding variables if required [32]. The proportion of fallers between groups will be compared using the relative risk statistic. Between-group comparisons of final test performance for the continuously-scored outcome measures will be made using General Linear Models (ANCOVA) controlled for pre-test performance. Baseline continuously-scored data will be compared between groups using the student t-test. Ordinally-scored data will be analysed for between group differences using the non-parametric Mann Whitney U statistic. An intention-to-treat approach will be used for all analyses.

Economic analysis will be undertaken in the manner used in previous falls prevention studies [33,34]. The total costs in intervention and control groups (including the cost of the exercise program, and costs of health and community service contacts) and falls rates, will be used to calculate an incremental cost per fall prevented in the intervention group compared with the control group. Bootstrapping will be used to estimate a distribution around costs and health outcomes and to calculate confidence intervals around the cost-effectiveness ratio; one-way sensitivity analyses will be conducted around key parameters.

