### Sample size

As fall rates will be compared between groups using incident rate ratios (IRR) from negative bionomial regression models [32] we conducted an analysis of statistical power using the nbpower command in the STATA software package. A total of 230 participants (115 per group) will be required to provide 80% power to detect as significant, at the 5% level, a 30% lower rate of falls for exercise subjects than control subjects (i. e. IRR = 0.70). We assumed the control group rate of falls would be 1 fall/person month over the 6-month follow-up period, a conservative estimate as the prospective cohort study [3] reported a falls rate of 1.6 falls/person month in a 12-month follow up of 113 people with PD.

The sample size of 230 will also be sufficient to detect between-group differences of 23% of control group values in the coordinated stability (balance) measure (assuming a control group mean of 18 and SD of 14) and 11% for knee extension strength (assuming a control group value of 16 kg and SD of 6). Both calculations are based on values found among fallers with PD [3] assuming 80% power of a two-sided test at the 5% level, a correlation between pre-and post measures of 0.7, and 15% dropouts.

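### The planned bootstrap confidence interval for cost per fall prevented can mislead when the fall difference is not clearly above zero, about 1 trial in 5 at the design effect

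*Protocol article*

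**What the plan says.** Under Statistical analysis, the protocol article says that total costs and fall rates "will be used to calculate an incremental cost per fall prevented in the intervention group compared with the control group". Uncertainty is handled in one sentence: "Bootstrapping will be used to estimate a distribution around costs and health outcomes and to calculate confidence intervals around the cost-effectiveness ratio". The same sentence adds sensitivity analyses that vary one parameter at a time. The general approach is said to follow two earlier falls prevention studies, which are cited but not reproduced. The article does not name the bootstrap interval method or say what will be reported if the fall difference is close to or below zero.

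The precision of the fall difference follows from Sample size, which fixes 230 participants, 115 in each arm, for 80% power. The target effect there is "at the 5% level, a 30% lower rate of falls for exercise subjects than control subjects", that is, a rate ratio of 0.70. The event rate behind it is also given: "We assumed the control group rate of falls would be 1 fall/person month over the 6-month follow-up period". No dispersion parameter is given. Cost-effectiveness is a declared aim in the Abstract, the Background and the Discussion.

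**The concern.** The plan chooses the ratio as the quantity that receives the confidence interval. A ratio of incremental cost to falls prevented behaves well only while the denominator stays away from zero on one side.

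When replicates straddle zero, two things go wrong. The ratio jumps between large positive and large negative values as the denominator crosses zero. A negative ratio also has two opposite meanings: cheaper with fewer falls (dominant), or dearer with more falls (dominated). Ranking replicates by ratio puts both at the same end of the scale. Percentile limits still come out as finite numbers, so nothing in the output warns the reader. The worst replicates can supply a lower limit that looks like a large saving per fall prevented.

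At stake is whether the trial's cost-effectiveness statement can be read when the fall effect is uncertain, which is when an interval is most needed.

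**Working it through.** **Inputs.** From Sample size: n = 115 per arm, 80% power, 5% level (taken as two-sided), rate ratio (IRR) 0.70, and control mean m0 = 1 fall per month × 6 months = 6. Then m1 = 6 × 0.70 = 4.2. The dispersion k is not stated.

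**Step 1: dispersion implied by the design.** For negative binomial regression, Var(log IRR) = (1/m0 + 1/m1 + 2k)/n. Eighty per cent power requires SE = |ln 0.70|/(1.960 + 0.842) = 0.3567/2.802 = 0.1273. Solving for k:

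k = (0.1273² × 115 − (1/6 + 1/4.2))/2 = (1.864 − 0.405)/2 ≈ 0.73.

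The stated 230 cannot be reproduced independently without k, so 0.73 is what that figure implies and not a check on it.

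**Step 2: precision of the denominator.** The SE of the difference in mean falls is sqrt((m0 + k·m0² + m1 + k·m1²)/n). At IRR 0.70 and k = 0.73 this is sqrt((32.28 + 17.08)/115) = 0.655. The expected difference is 6 − 4.2 = 1.8, or 1.8/0.655 = 2.75 SE from zero.

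**Step 3: how often replicates reach the wrong side.** Within one trial, the share of replicates at or below zero exceeds 2.5% when the observed difference is less than 1.96 SE. Across trials this has probability Φ(1.96 − difference/SE).

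| k | True IRR | Difference | SE | Chance that over 2.5% of replicates have a wrong-sign denominator |
|---|---|---|---|---|
| 0.73 (implied) | 0.70 | 1.8 | 0.655 | 22% |
| 0.73 | 0.80 | 1.2 | 0.685 | 58% |
| 0.73 | 0.85 | 0.9 | 0.700 | 75% |
| 1.5 (assumed) | 0.70 | 1.8 | 0.888 | 47% |
| 3 (assumed) | 0.70 | 1.8 | 1.220 | 69% |

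A direct simulation (1000 trials, 1000 resamples each) gave 20% for the first row, 75% for the third, 43% for the fourth and 66% for the fifth. On the log-rate scale the first row is exactly 20%, because a trial powered at 80% misses significance one time in five. About 1 in 5 is therefore a fair summary at the design effect.

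Two related quantities should be kept apart. At IRR 0.70 and k = 0.73, the chance that the trial's point estimate has the wrong sign is Φ(−2.75) = 0.3%. The mean share of wrong-sign replicates across trials is Φ(−2.75/√2) = 2.6% (2.3% in simulation).

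**Step 4: what the interval can look like.** The documents give no cost figures, so assume an extra cost of 1000 with SE 300, independent of falls, and an observed IRR of 0.85 at k = 0.73. The point ratio is 1000/0.9 = 1111. The 2.5 and 97.5 percentiles of the ranked ratios are about −9,000 and +11,000. About 10% of replicates have a negative ratio, and nearly all of these are dearer with more falls. A reader would take the lower limit for a saving.

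**The case against.** The strongest reply has four parts.

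- **The article condenses a fuller plan.** How to report the ratio in an awkward case is commonly left to that plan, and the two cited studies may supply a rule. This stands as regards the missing rule, which is not itself the complaint. The choice of the ratio as the target of the confidence interval is stated text.
- **No percentile method is named.** Replicates could be ordered by their position on the cost-effectiveness plane, which keeps dominant and dominated results apart. This also stands: the defect shown above belongs to intervals formed by ranking ratios, and the article does not say that this will be done.
- **The same sentence already plans a distribution of costs and outcomes.** Net benefit or a plane could be drawn from it. That is true, and it is why the change is cheap, but the only interval the text commits to is the one on the ratio.
- **The design makes trouble the exception.** With IRR 0.70 and 80% power, about four trials in five would have a denominator clearly above zero and a readable ratio interval. This stands.

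A reader might infer that an uninterpretable interval is likely at this trial's precision, or that a ratio interval is always invalid. The documents support neither. The first needs a smaller effect than the design effect or more dispersion than the implied 0.73, and no k is stated. A value near 3.8 can be obtained by combining the cohort mean of 1.6 × 12 = 19.2 falls a year with 100 − 68 = 32% non-fallers. However, the 68% is an upper figure from several studies, and this trial enrols fallers or people at risk, so that value should not be taken as the trial's own.

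**Conclusion.** The point holds as a minor one on a secondary analysis. A confidence interval on cost per fall prevented is readable when the fall difference is clearly positive and can mislead when it is not. On the design's figures, the misleading case arises in about 1 trial in 5. It becomes the usual case if the true effect is smaller (58% at IRR 0.80, 75% at IRR 0.85). It is close to an even chance at the design effect if k is 1.5 (47%).

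These figures rest on a negative binomial model, full follow-up of 115 per arm, a two-sided 5% level, an unadjusted fall difference, a normal approximation confirmed by simulation where it was run, and k inferred from the stated power. Values of k above 0.73 are assumptions. The primary comparison of fall rates is unaffected.

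**What to change.** Keep the joint bootstrap of costs and falls, and change the summary drawn from it:

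- Base inference on incremental net benefit, λ × (falls prevented) − (incremental cost), with its bootstrap interval over a stated range of willingness to pay λ per fall prevented. This quantity is linear in both differences, so it has no discontinuity at zero.
- Show the replicates on a cost-effectiveness plane and summarise them in an acceptability curve.
- Report the incremental cost per fall prevented as a point estimate, with a confidence interval only if the interval for the fall difference excludes zero.

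The cost is a few lines of wording. No new data and no extra resampling are needed. The one drawback is that results must be read across a range of λ, because the protocol article gives no accepted value for a fall prevented. Settling this before the data are seen also avoids a later choice of summary that could be influenced by the result.

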### Sample size

As fall rates will be compared between groups using incident rate ratios (IRR) from negative bionomial regression models [32] we conducted an analysis of statistical power using the nbpower command in the STATA software package. A total of 230 participants (115 per group) will be required to provide 80% power to detect as significant, at the 5% level, a 30% lower rate of falls for exercise subjects than control subjects (i. e. IRR = 0.70). We assumed the control group rate of falls would be 1 fall/person month over the 6-month follow-up period, a conservative estimate as the prospective cohort study [3] reported a falls rate of 1.6 falls/person month in a 12-month follow up of 113 people with PD.

The sample size of 230 will also be sufficient to detect between-group differences of 23% of control group values in the coordinated stability (balance) measure (assuming a control group mean of 18 and SD of 14) and 11% for knee extension strength (assuming a control group value of 16 kg and SD of 6). Both calculations are based on values found among fallers with PD [3] assuming 80% power of a two-sided test at the 5% level, a correlation between pre-and post measures of 0.7, and 15% dropouts.

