## Background

The number of persons with Parkinson's disease over age 50 in Western Europe's five most populous nations was up to 4.6 million in 2005, and this will double to up to 9.3 million by 2030 [1]. Over 100,000 Australians are currently living with Parkinson's disease [2] and in line with estimates from Western Europe this number is also expected to double by 2030 [1]. Since the most common age of onset is 50–60 years and life expectancy is near normal, people with Parkinson's disease suffer the debilitating consequences of the disease over decades.

The mainstay of medical treatment for Parkinson's disease is pharmacological therapy to boost depleted dopamine levels. Despite optimal medication, people with Parkinson's disease living in the community experience frequent and recurrent falls with devastating consequences. Up to 68% of people with Parkinson's disease will fall and up to 46% of people with Parkinson's disease will experience recurrent falls each year [3-6]. These rates are around twice of those in the general older population [6]. In addition, a 12-month prospective study (n = 113) found that 27% of people with Parkinson's disease fell at least once each month and 15% fell at least once a week [3].

Among people with Parkinson disease, as many as 65% of fallers will experience an injury secondary to their falls, 33% will suffer a fracture and 75% of falls will lead to use of a health care service [7]. Falls and related fractures are the most common secondary reason that people with Parkinson's disease are admitted to hospital [8]. These falls have devastating consequences and are accompanied by pain, reduced mobility and unacceptably high levels of caregiver stress. Fear of falling is also greater in community-dwelling people with Parkinson's disease than healthy controls [9]. This results in restriction of activities, compromising quality of life and predisposing to secondary reductions in muscle strength and cardiovascular fitness.

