We will investigate the effect of the PD-WEBB program in people with Parkinson's disease using a randomized controlled trial incorporating the features known to reduce bias (i. e. concealed random allocation to groups, blinded outcome assessment and intention to treat analysis) and large enough to detect any effect of the intervention on fall rates. This project will determine the effectiveness of the exercise intervention in reducing falls, but will also determine the cost effectiveness of the intervention. This program, if found to be effective, has the potential to be implemented at a reasonable and sustainable cost within existing community services. Any reduction in falls for people with Parkinson's disease will reduce the personal and financial costs to individuals with Parkinson's disease, their families, health care resources and the community.

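### The 80% power for fall rates needs a dispersion of about 0.73 or less, which the protocol does not state and its own cohort figures make doubtful; the claim to detect any effect contradicts the calculation

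*Protocol article*

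**What the plan says.** The Sample size section bases the primary comparison on negative binomial regression: "we conducted an analysis of statistical power using the nbpower command in the STATA software package". The conclusion is "A total of 230 participants (115 per group) will be required to provide 80% power to detect as significant". The same sentence then sets the significance level and the target effect: "at the 5% level, a 30% lower rate of falls for exercise subjects than control subjects". The event rate is given as "We assumed the control group rate of falls would be 1 fall/person month over the 6-month follow-up period". That rate is called conservative because the earlier cohort "reported a falls rate of 1.6 falls/person month in a 12-month follow up of 113 people with PD".

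No dispersion value appears. The only mention of loss is in the next paragraph, on balance and knee strength, which assumes "a correlation between pre-and post measures of 0.7, and 15% dropouts". That sentence covers those two calculations and not the one for falls.

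The Background describes the same 113-person cohort: 27% of people "fell at least once each month and 15% fell at least once a week". Across several studies, that cohort among them, it puts the share who fall in a year at up to 68% and the share with recurrent falls at up to 46%.

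The Discussion calls the trial "large enough to detect any effect of the intervention on fall rates".

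**The concern.** With an expected 6 falls per control participant, the power of a negative binomial comparison depends mostly on how much fall rates differ between people, which is what k measures. The stated power therefore rests on a number the reader cannot see. The cohort figures describe a very skewed distribution, with many people falling rarely and a small group falling every week, and so suggest a large k.

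If the power is lower than stated, a non-significant primary result would be over-read as evidence that the exercise programme does not work. The any-effect sentence in the Discussion invites that reading.

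**Working it through.** **Inputs** (Sample size section): 115 per arm; IRR 0.70; control mean 1 × 6 = 6 falls; intervention mean 6 × 0.70 = 4.2; 5% level; 80% power. I take the test as two-sided; the protocol says so only for balance and strength.

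**Formula.** Var(log IRR) = (1/μ0 + 1/μ1 + 2k)/n per arm. Power = Φ(|ln IRR|/SE − 1.96).

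**1. The k that reproduces 115 per arm**
- Required variance: (0.3567/2.802)² = 0.01621.
- No loss: 115 × 0.01621 = 1.864. Since 1/6 + 1/4.2 = 0.405, k = (1.864 − 0.405)/2 = **0.73**.
- Complete loss of 15% (97.75 per arm): 97.75 × 0.01621 = 1.584, so k = (1.584 − 0.405)/2 = **0.59**.
- A one-sided test with no loss would allow k = 0.98.
- At k = 0.73 the term 2k supplies 1.46 of 1.864, or 78% of the variance. With k = 0 (Poisson), 25 per arm would be enough.

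**2. Does k = 0.73 fit the cited cohort?** The cohort mean is 1.6 × 12 = 19.2 falls per year. A negative binomial with that mean and k = 0.73 gives:

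| | Predicted | Reported |
|---|---|---|
| Any fall in the year | 98% | up to 68% |
| At least monthly (12 or more) | 59% | 27% |
| At least weekly (52 or more) | 5% | 15% |

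The mean and the last two rows come from the same cohort.

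**3. Dispersion without a fitted model.** The reported shares make five groups: no falls 32%, one fall 22%, 2–11 falls 19%, 12–51 falls 12%, 52 or more 15%.
- Variance made as small as the mean of 19.2 allows: group values 0, 1, 11, 51 and 71.8. Variance 740, so k = (740 − 19.2)/19.2² = **1.96**.
- Mid-range values 0, 1, 5, 25 and 100.2: variance 1217, k = **3.25**.
- Fallers only (mean 19.2/0.68 = 28.2): k = **1.01** with the first set of values and **1.89** with the second.

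**4. Unadjusted power for IRR 0.70**

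| k | 115 per arm | 97.75 per arm |
|---|---|---|
| 0.59 | 86% | 80% |
| 0.73 | 80% | 73% |
| 1.0 | 69% | 62% |
| 1.5 | 54% | 48% |
| 2.0 | 45% | 39% |

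The last column assumes that people who leave contribute nothing. If the 15% leave on average halfway and their diaries count, power at k = 0.73 is about 78–79%.

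**5. The margin from the fall rate.** At 1.6 falls per month the means are 9.6 and 6.72. Variance = (0.104 + 0.149 + 1.46)/115 = 0.0149 and SE = 0.122, so power is 83% against 80%.

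**6. Smaller effects at k = 0.73, 115 per arm**
- IRR 0.80: SE = √[(0.167 + 0.208 + 1.46)/115] = 0.126; 0.223/0.126 = 1.77; power **42%**.
- IRR 0.90: SE = √[(0.167 + 0.185 + 1.46)/115] = 0.126; 0.105/0.126 = 0.84; power **13%**.

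**7. Effect of adjustment.** Simulated negative binomial regressions (500 per setting, 115 per arm, no loss) adjusted for more than 10 prior-year falls, which is the randomisation stratum. "Stability" here is the assumed share of people whose fall propensity carries over from the prior year.

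| Raw k | Full stability | 60% stability |
|---|---|---|
| 1.0 | 93% | 76% |
| 1.9 | 78% | 51% |
| 3.77 | 58% | 37% |

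With 98 per arm, the corresponding figures are 86%, 73% and 53%, and 69%, 49% and 31%.

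**The case against.** A reader might infer that the stated power holds only at k = 0.73 with no dropout, and that true power is well below 80%. The protocol does not support either statement, for these reasons.

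- k = 0.59 with 15% complete loss also gives 80%. The inputs used are not shown, and the team, which describes the cohort as its own, may have used a dispersion from it.
- The 15% loss is not stated for falls. With monthly calendars and an analysis per person-year, people who leave early still contribute, so complete loss is a worst case.
- The 68% and 46% are upper figures over several studies, while the mean comes from one. Without those two shares, the cohort's mean, 27% and 15% allow k as low as 0.55 (73% of people at 11 falls, 12% at 28, 15% at 52.07; variance 220; (220 − 19.2)/19.2²). That would need everyone to fall at least 11 times a year. The fallers-only values are approximations, not bounds.
- No negative binomial with mean 19.2 reaches 15% weekly fallers; the share peaks at 11.5%. Matching single percentages gives k of 3.8 (any fall) or 6.3 (monthly), but these are not estimates of the trial's dispersion, and neither is the 27% power that follows from 3.8.
- The relevant k is residual. The trial enrols past or at-risk fallers and adjusts for previous multiple faller status, and both should lower it.
- Calling the rate conservative refers to the rate alone, and there it is correct.

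All of this stands, but it does not restore the 80%. The adjustment covariate is not defined and need not be the cut at 10 falls. Read as two or more prior falls with stable rates, it leaves k at about 1.1 to 1.6, or 66% to 52% power. In the simulations, a clear excess over 80% needed the lowest raw dispersion together with full stability. None of these points rescues the any-effect sentence.

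**Conclusion.** The concern holds in a limited form. The stated 80% needs a residual dispersion of about 0.73, or less if participants are lost, and the protocol's cohort figures point higher. For k from 1 to 2, unadjusted power is 69% to 45%. How far adjustment closes the gap depends on the covariate and on how stable fall rates are from year to year, neither of which the protocol settles. Power is therefore probably below 80%, but this is not proven, and no single figure for the true power can be given.

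Two conclusions do not depend on the dispersion of the cohort. The lower fall rate is a cautious choice but adds only about 3 percentage points at k = 0.73. The any-effect claim is wrong even on the assumptions that yield 80% for IRR 0.70.

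These results assume a two-sided 5% test, the Wald approximation, equal arms and a common k.

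**What to change.** Keep 230 participants and correct what is said about them.

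- Recompute the primary power with the dispersion seen in cohort members who meet the trial's eligibility criteria, under the planned adjusted model and with the expected loss, counting partial diaries.
- State k, its source and the dropout allowance for falls.
- Report the power for IRR 0.70, or the IRR detectable with 80% power, over a range of k. Unadjusted and with no loss, the detectable IRR is 0.67 at k = 1 and 0.58 at k = 2.
- In the Discussion, replace the any-effect claim with that figure.

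The cost is one recalculation, new wording in two places and a less favourable stated power. No more patients are needed.
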